**G. Location where study will be performed:**

The informed consent interview and enrollment survey will be conducted at the participant's hospital of enrollment, in a private room. CATSystem data entry at enrollment and at all subsequent participant encounters will also be conducted at the hospital of the participant's enrollment. Cervical cancer screening and most treatments (thermocauterization, cryotherapy) will be conducted at the participant's hospital of enrollment. In instances where participants need more intensive treatment (chemotherapy, radiation) they may be referred to a higher level facility, where these services will be performed and documented within the CATSystem.

Paper-based records (informed consent, paper surveys) will be stored in a locked filing cabinet at the study hospital. They will be collected by Co-I [name] on a quarterly basis and then be stored at the Global Health Innovations office in Nairobi until study completion.

**H. Collaboration (with another institution, if applicable):** This is a collaborative effort between the University of Kansas Medical Center (KUMC), American Academy of Family Physicians (AAFP), Children's Mercy Hospital (CMH), University of Michigan (UMich), and Global Health Innovations Kenya (GHI). KUMC will serve as the lead IRB for the study and AAFP, CMH, and UMich will rely on their approval. Study approval will also be sought by GHI through the Kenya Medical Research Institute. As the in-country approving IRB, consent forms will be drafted using their template.

**I. Single IRB Review for a Multi-site study (if applicable):**

1. **For which sites will KUMC serve as the IRB of record?** KUMC, AAFP, CMH, UMich
2. **Indicate which study activities will occur at each site. If all study procedures will be identical across study sites, state this.** The table below outlines the sites participating in this study and their roles in study implementation

|                             | Organization                        | Study Role                                                                                                                                                                             |
|-----------------------------|-------------------------------------|----------------------------------------------------------------------------------------------------------------------------------------------------------------------------------------|
| Administrative Sites | University of Kansas Medical Center | Annual Conflict of Interest and Human Subjects Research Certification for all KUMC and GHI study members; study design, implementation and management, data analysis and dissemination |
|                             | Kenya Medical Research Institute    | Institutional Review Board and adverse event monitoring; liaison with hospital and government administrations in study regions; long term storage of study records                     |
|                             | Children's Mercy Hospital; Kansas   | Support for study design, implementation, and data analysis                                                                                                                            |

|                                       |                                 |                                                                                                                                                                          |
|---------------------------------------|---------------------------------|--------------------------------------------------------------------------------------------------------------------------------------------------------------------------|
|                                       | City, MO (CMH)                  |                                                                                                                                                                          |
|                                       | University of Michigan          | Support for study design, implementation, and data analysis                                                                                                              |
| Data Coordinating Sites        | Global Health Innovations (GHI) | CATSystem technical support, oversight of Study Coordinators monitoring daily study activities (informed consent, data collection, patient follow-up) at all study sites |
| Enrollment/Participating Sites | 10 Kenyan health facilities     | CATSystem and study enrollment, HIV care service provision, onsite VL sample collection, temporary storage of study records                                              |

3. **Describe how you will assess the capacity of each site to perform the research (e.g., expertise, staffing, space, equipment, etc.) If applicable, include site evaluation tools in your IRB submission.** We will hire and train one full time research assistant for each study hospital. Each RA will be trained to conduct study procedures specific to the study arm allocation. RAs have demonstrated effective and reliable HITSystem use in our prior studies and programmatic work. At all sites, RAs will assess eligibility, conduct informed consent procedures and surveys, and facilitate participant follow up. At sites implementing CATSystem, RAs will be the primary persons to enter and routinely update patient data. RAs also will lead patient outreach and follow-up efforts (phone or texting via CATSystem). Site Coordinators will routinely visit each study hospital to provide supportive supervision to ensure adherence to study protocols.
4. **Describe how the lead investigators will ensure that all participating sites use the IRB-approved version of the protocol, consent, recruitment materials and other study documents.** Hard and soft copies of all study related documents will be provided to participating sites. If changes are made to any of the materials, the newer versions will be provided as soon as IRB approval is received. At each visit, site coordinators will ensure that the most recent version of documents are being used. At site visits, site coordinators will also collect the informed consents from the site to give to Co-I [name] for storage. [name] will review all study documents upon receipt to ensure that the appropriate version is being used and that the forms are being filled out correctly. If she has any concerns, she will work with the site and the site coordinator to schedule a follow up training. Since data collection occurs through the web-based CATSystem, all changes will be automatically and immediately applied across study sites, ensuring that the most recent version of the tool is being used by all sites.
5. **Describe how the lead investigators will communicate with and disseminate new information to other sites (e.g., training meetings, regularly-scheduled conference calls, notifications, etc.)** The lead investigator will communicate with each of the sites in the following ways:
  - Prior to study launch, a startup training will provided to all study sites. This training will cover purpose of the study, conducting informed consent, enrolling participants, and using the site's designated point of care testing system.
  - Twice monthly calls between the US-based team, Kenya-based Co-Is, and the site coordinators assigned to each study site will allow the lead investigators to check up on study progress and communicate new information to site coordinators.

- Site coordinators will make monthly visits to study sites to check up on study progress and disseminate any relevant information to clinical staff. Additional phone or email follow up between study sites and site coordinators will occur to address issues that come up.
- Email or additional calls between US-based personnel, Kenya-based personnel, and study sites will occur, as necessary.

6. **Describe how the lead investigator will assess protocol compliance, unanticipated problems and adverse events at other sites.** US-based study staff will review study-related material (including informed consents and data collected through the CATSystem) at least quarterly. Any concerns with the consent forms or the data collection will be immediately addressed. Monthly calls between US and Kenya-based research staff will allow site coordinators to check in with [name] after each site visit to discuss study progress and concerns. [name] will make quarterly visits to all study sites to assess protocol compliance and address any issues and adverse events. Staff at each study site will have [name]'s and their designated site coordinator's phone numbers and email addresses, allowing them to contact research personnel if any questions or issues arise. A designated field in the CATSystem and control site data sheets allows clinical and research staff to document any adverse events.
7. **Name the member of the KUMC study team who will be the point of contact to coordinate oversight and communication with the sites.** PI [name] will be the point of contact to coordinate oversight and communication with the sites.

**J. Community-Based Participatory Research (if applicable)**

N/A

**K. Personnel who will conduct the study, including:**

1. Indicate, by title, who will be present during study procedure(s): Clinical staff, research assistants, and/or site coordinator
2. Primary responsibility for the following activities, for example:
  - a. Determining eligibility: Research assistant
  - b. Obtaining informed consent: Research assistant
  - c. Providing on-going information to the study sponsor and the IRB: PIs [name] and [name]
  - d. Maintaining participant's research records: Research assistant, site coordinator, Co-I [name]
  - e. Completing physical examination: Clinical staff
  - f. Taking vital signs, height, weight: Clinical staff
  - g. Drawing / collecting laboratory specimens: Clinical staff
  - h. Performing / conducting tests, procedures, interventions, questionnaires: Clinical staff or Research Assistant
  - i. Completing study data forms: Research assistant and/or study coordinator
  - j. Managing study database: Study Statistician

**L. Assessment of Subject Safety and Development of a Data and Safety Monitoring Plan**

An external DSMB will be established to review and evaluate the accumulated study data for participant safety, study conduct, and progress on an annual basis. The DSMB membership will include a minimum of three members: one biostatistician, one epidemiologist, and one or more clinician with expertise in obstetrics, gynecology, oncology and cervical cancer care in Kenya. All members will have expertise in the conduct and methodology of clinical trials. Given geographic distances, DSMB communication will be conducted via email and phone, with annual meetings conducted using web-based conferencing. All serious adverse events will be reported to IRBs in both countries and to the DSMB. Based on these assessments, the DSMB will make recommendations regarding the continuation, modification or early termination of the study. The DSMB will establish early stopping protocols prior to study initiation.

**III. Subject Participation**

**A. Recruitment:** All women who receive cervical cancer screening at study hospitals will be offered enrollment into the study. Clinical staff or the research assistant may identify eligible women from the Maternal and Child Health/Family Planning (MCH/FP) or comprehensive care centers (CCC). Once identified, the research assistant assigned to each site will inform eligible women about the purpose of the study, will describe risk/benefits of the study, and will describe what to expect from participation in the study before asking women if they'd like to enroll in the study. At control sites, the standard of care services will be described to participants. At intervention sites, the standard of care services and the unique communication features of the CATSystem will be described to patients. Eligible women will sign a written informed consent form in either Kiswahili or English (per the participant's preference) prior to enrollment. If a woman is non-literate, a thumbprint will be used in lieu of a written signature. Upon enrollment, the RA will conduct a brief enrollment survey with each participant. Participant will be remunerated \$2.00 for participating in the enrollment survey, in appreciation of their time.

**B. Screening Interview/questionnaire:** N/A

**C. Informed consent process and timing of obtaining of consent**

All participants will be informed of the purpose of the research, including the potential benefits and risks of CC screening and treatment and, at CATSystem-implementing sites, the unique communication features of the CATSystem. The RA will go over the informed consent with each woman and then allow her to read it over on her own. RA will explain that all participants have the right to discontinue participation at any time and that women who decline study participation will access standard of care cervical cancer screening and treatment services. At CATSystem study sites, caregivers declining study participation can also choose to be tracked in the CATSystem without providing additional samples for VL tests.

Prior to a request for written informed consent, women will be asked to summarize what they've been told/read to ensure comprehension. Women will then be asked if they would like to enroll with their infants by: a) providing their cell phone contact and/or tracing map from the hospital to their residence to facilitate follow up and (b) allowing their patient information to be entered and tracked in the CATSystem (at CATSystem sites only). Women who are non-literate will have the option of using a thumb-print in lieu of a signature for study consent.

Girls between the ages of 16 and 18 are eligible for inclusion in this study, with consent from a legal guardian and assent from the girl. RAs will take additional time with these young participants to

ensure comprehension, emphasizing that participation is optional and is not a requirement for receiving standard of care cervical cancer screening and treatment services.

The contact number of the Site Coordinator and in-country PI will be provided to all who agree to participate. Participants will be encouraged to call this number if they have questions about their participation in the study. IRB approval will be sought from an institution in Kenya and the University of Kansas Medical Center.

- D. Alternatives to Participation:** Women who choose not to participate in the study will receive standard cervical cancer screening and treatment at the hospital, without CATSystem tracking and/or additional study measures (e.g. enrollment survey). At intervention hospitals, women who choose not to participate in the study can still opt-in to CATSystem enrollment programmatically and choose to have their data excluded from study analyses. Women will be made aware of these alternatives during the informed consent process.
- E. Costs to Subjects:** N/A
- F. How new information will be conveyed to the study subject and how it will be documented:** Providers or the site coordinator will inform participants of new information at their next clinic appointment. Documentation of all new information or procedures will be kept in the study records. Documentation of a woman's notification of new information will be noted in the "comments" field of the woman's CATSystem entry.
- G. Payment, including a prorated plan for payment:** Upon enrollment, the RA will conduct a brief enrollment survey with each participant. Participant will be remunerated \$1.00 for participating in the enrollment survey, in appreciation of their time. Participants in Aim 2 qualitative components will receive \$5.00 in remuneration to support travel to/from the hospital and in appreciation of their time. Travel costs will not be reimbursed
- H. Payment for a research-related injury:** N/A

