## Procedures.

**Data Collection and Security:** At all study sites, patient-specific data including demographics; phone number and patient tracing information; patient health history; dates screened and treated; lab processing of PAP and biopsy tests, lab results, and follow-up screens will be entered directly into CATSystem by team members on password secured computers. The CATSystem was built in compliance with Kenya's 2019 Data Protection Act guidelines, is password protected, and maintains data for each client using numeric IDs to protect identities of participants and data exports in Excel. The system has been rigorously vetted by the KUMC Office of Information Security for vulnerabilities and passed both Security Headers and SSL labs test with a score of A and A+ respectively. At SOC sites, all clinical and CC screening service-related data will be collected in existing paper-based registries by health care providers per routine services. To prevent unintended intervention from health workers at control sites (reviewing clinical registers and entering participant data more comprehensively than they would in SOC setting), site coordinators will review paper registries at each control site visit and electronically enter patients' CC screening and treatment uptake data, using multiple sources (MCH, CCC, lab) to triangulate data. A parallel 'look-alike CATSystem' with all alerts, SMS, and patient tracking algorithms turned off, will be used for SOC data collection, to facilitate accurate, complete, and comparable data across arms. This process has been effectively used in our previous and current cRCT studies.

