The proportion of screened women with a positive result ranged between 3.4% (53/1576) during the SOC period and 7.1% (39/550) during the intervention period. **To guide enrollment targets, we will assume a positive screen rate of 5%, which would require enrollment of at least n=600 women per cluster to result in 30 women with a positive screen. We will enroll an additional 10% to account for attrition due to relocation, transfer of health facility or death.** During our pilot study, we enrolled 552 patients at the pilot facility over the span of 15 months, however, several months were impacted by Covid-19 restrictions at the health facility (n=3) or a clinical worker strike (n=1) when enrollment numbers dropped from an average of 53 to 24 patients per month. We thus estimate the potential to have enrolled up to 795 patients under more normal conditions. We also anticipate that monthly enrollment numbers may decrease over the 24-month period, given that once a woman has been screened and/or treated, their next screening appointment per guidelines would be within 3 to 5 years; thus fewer women at the health facility will be eligible for screening over the course of the study. With this in mind, **we expect a 24 month enrollment**

**period will be adequate to reach a total of 660 participants at each hospital (660 x 10 sites= 6,600 study participants).**

**Missing data; multiple testing.** Taking an intent-to-treat approach, rather than exclude participants who drop out from analyses we will carry out and compare two analyses, one where dropouts are classified as not receiving treatment, and another where inverse probability of attrition weighting is used to adjust for participants lost to attrition. Missing data on explanatory variables will be imputed using stochastic regression imputation or, if the rate of missing data exceeds 1%, using multiple imputation by chained equations. Consistent with guidance from the statistics community, we will focus on effect sizes and their confidence intervals rather than treating  $p < 0.05$  as a dichotomous indicator of whether an effect is practically important and classifying results as “significant” or “not significant” on this basis. Model selection processes that exploit chance will be avoided.

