3. **Social risk:** Loss of confidentiality and stigma are concerns. In a setting in which a woman may not have disclosed her cervical cancer screening status to her partner, inadvertent disclosure is a concern. Participants could be treated unfairly or discriminated against, or could face problems being accepted by their partner, family or community. This is a greater concern at intervention sites using the CATSystem, as the CATSystem will send SMS to women to prompt return to the hospital. To protect confidentiality, the following steps will be taken: Study staff will be trained regarding the need to strictly protect confidentiality; this will also be reinforced with the clinic staff. Prior to starting the study, we will meet with clinic staff and peer counselors to identify any additional strategies that could be taken in that particular setting to help improve participant confidentiality. This includes strict adherence to protocols for the content of CATSystem text messages and procedures for those engaged in patient tracing in the community. Messages sent by the CATSystem were designed to protect patient confidentiality, by not referring to cervical cancer. Loss of confidentiality is also a risk for participants of the focus group discussions and surveys. While facilitators will emphasize the need for confidentiality amongst participants, confidentiality cannot be fully guaranteed in a focus group setting. This will be explained to participants.
4. **Economic risk:** The CATSystem will prompt patient retention in standard of care clinical services; however, will not financially support the provision of these services. In instances where women are prompted to return for services by the CATSystem – but would not have otherwise returned – they will be responsible for covering the costs of the services they receive.
5. **Potential benefit of participating in the study:** The potential for individual benefit from study participation exists, particularly among women enrolled in the intervention arm. In preliminary data, the CATSystem improved retention in cervical cancer screening and treatment. Early detection of

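### Enrolment at CATSystem hospitals is bundled with agreeing to be tracked in the CATSystem, which SOC women are not asked to accept; the resulting unequal selection may bias the primary comparison

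*Protocol*

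**What the plan says.** The study statistician allocates one hospital in each matched pair to the intervention (Protocol II.D). Women are then approached one by one. At intervention hospitals the CATSystem's communication features are described to them; at control hospitals only standard services are (III.A).

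Section III.C describes enrolment as two acts:

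- (a) "providing their cell phone contact and/or tracing map from the hospital to their residence to facilitate follow up", with no restriction by arm;
- (b) "allowing their patient information to be entered and tracked in the CATSystem (at CATSystem sites only").

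Section III.D offers one alternative at intervention hospitals: "At intervention hospitals, women who choose not to participate in the study can still opt-in to CATSystem enrollment programmatically", with their data left out of the study analyses. No section offers the opposite choice, taking part in the study without being tracked.

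On loss of confidentiality and stigma, section II.F says "This is a greater concern at intervention sites using the CATSystem", and gives the SMS prompts as the reason.

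For SOC data, section II.B (Procedures) uses a copy of the system "with all alerts, SMS, and patient tracking algorithms turned off, will be used for SOC data collection".

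The missing-data text in II.C reads: "Taking an intent-to-treat approach, rather than exclude participants who drop out from analyses". It then gives two ways of handling dropouts.

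**The concern.** In a cluster trial that recruits after allocation, the arms stay comparable only if the same kind of woman enrols in each. Here the consent condition itself differs by arm. At CATSystem hospitals, agreeing to the study means agreeing to the intervention. At SOC hospitals it does not.

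The women affected are those who would give contact details and let their data be used, but do not want CATSystem tracking or SMS. More of them may be missing from the CATSystem arm than from the SOC arm. If their willingness to be tracked is related to completing treatment, which is the primary outcome, the treated proportion among enrolled women shifts in one arm for a reason unrelated to what the CATSystem does.

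Nothing in the stated analysis corrects this. The intention-to-treat text and the attrition weighting concern women who enrolled and then left. Covariates and propensity weighting (II.C) work on measured characteristics of enrolled women. The random site intercept allows for clustering, not for a systematic difference between arms in who enrols.

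**Working it through.** **Inputs from the protocol (II.C, sample size):** treatment rates 0.10 (SOC) and 0.35 (CATSystem); 5 clusters of 30 screen-positive women per arm; one-sided α = 0.025; ICC 0.05 in the clusterPower check, with stated power 85.9%.

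**Assumptions, because the protocol gives no figures:** r is the extra share of screen-positive women who refuse at CATSystem hospitals only because of tracking or SMS, taken as 10%-20%. f is their chance of treatment relative to the average, taken as 0 to 1.5. Each cluster still supplies 30 enrolled screen-positive women.

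**Step 1. Reproduce the stated power.** Design effect = 1 + 29 × 0.05 = 2.45.
SE = √[(0.10 × 0.90 + 0.35 × 0.65) × 2.45 / 150] = 0.0720.
Non-centrality = 0.25 / 0.0720 = 3.47. With 8 degrees of freedom the critical value is 2.306, and the non-central t gives power 85.9%, as stated. The same formula is used below.

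**Step 2. Rate among women who enrol.** If the average over all women is p and refusers have rate f·p, the enrolled rate q satisfies (1 − r)q + r·f·p = p. So q = p(1 − r·f)/(1 − r).

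**Step 3. No true effect, p = 0.10 in both arms.** The SOC arm stays at 0.10; the CATSystem arm shows q.

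| f | r | q | Spurious OR | One-sided error |
|---|---|---|---|---|
| 0 (never treated) | 10% | 0.111 | 1.13 | 3.7% |
| 0 | 20% | 0.125 | 1.29 | 5.8% |
| 0.5 | 10% | 0.106 | 1.06 | 3.1% |
| 0.5 | 20% | 0.1125 | 1.14 | 3.9% |
| 1 | any | 0.100 | 1.00 | 2.5% |
| 1.5 | 10% | 0.094 | 0.94 | 2.0% |
| 1.5 | 20% | 0.0875 | 0.86 | 1.5% |

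Example (f = 0.5, r = 20%): q = 0.10 × 0.90 / 0.80 = 0.1125; OR = (0.1125/0.8875) / (0.10/0.90) = 1.14.

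**Step 4. Planned effect, 0.10 against 0.35.** The true OR is (0.35/0.65)/(0.10/0.90) = 4.85. For r = 10%-20% it would be observed as 5.73-7.00 (f = 0), 5.27-5.85 (f = 0.5), 4.85 (f = 1), or 4.44-3.97 (f = 1.5).

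**Step 5. Allow for act (a).** Suppose half of the women unwilling to be tracked also refuse at SOC hospitals because of (a). The SOC rate then becomes p(1 − r·f/2)/(1 − r/2). With no true effect, r = 10%-20% and f = 0, the OR is 1.06-1.14 and the error 3.1%-4.0%. If all of them refuse in both arms, the OR is 1.00.

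**The case against.** The strongest reply is that SOC women are filtered too. Act (a) asks for a phone contact or tracing map in both arms. Phone access and the ability to read SMS are eligibility criteria everywhere (II.D). Section II.I, item 3, adds: "At all sites, RAs will assess eligibility, conduct informed consent procedures and surveys, and facilitate participant follow up". This stands. A reader might infer that women unwilling to be followed leave only the CATSystem arm. The documents do not support that: the unequal loss is confined to women who accept (a) and decline (b).

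A reader might also infer that the effect is biased, and biased toward the CATSystem. Neither is shown. No document gives refusal by arm or refusers' outcomes, and the direction reverses if refusers do better than average. Same-day onsite treatment, the stated ideal for precancerous lesions, depends little on later tracing, which weakens the link. It does not remove it, because the outcome text also covers rescreening, referral and treatment follow-up.

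The protocol also softens the motive to refuse. Messages avoid mentioning cervical cancer (II.F) and can be replaced by neutral words or numbers (II.D). That argues for a small r, not for zero.

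Two further readings should be set aside. Taking 0.35 as the no-effect rate gives larger error rates, but the protocol assumes 0.10 under SOC. And one might infer that SOC women's records go into the look-alike system without their permission. The consent forms are not available to check this, and the copy has its tracking switched off, so no such conflict can be established.

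Finally, III.C carries wording from another study (infants, caregivers, viral-load samples), so the clause may not be a deliberate enrolment rule. That is a further reason to restate it for this trial.

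**Conclusion.** The point holds as a risk of unequal selection built into the consent condition and not corrected by the stated analysis. Its size is unknown and its direction depends on how refusers would have fared.

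Under the assumed 10%-20% extra refusal at the protocol's SOC rate, the spurious odds ratio is modest: 1.06-1.14 when refusers have half the average success, and 1.13-1.29 in the extreme case of no refuser being treated. The one-sided error moves from 2.5% to between 3.1% and 5.8%. That is small beside the planned odds ratio of 4.85 and would not by itself create an effect of that size, but it could distort the estimate and its interval. The stated power of 85.9% is reproduced and is not in question.

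The change is worth making because it is cheap now, and a later analysis cannot recover outcomes for women the consent rule kept out.

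**What to change.** Rewrite the enrolment paragraph in Protocol III.C:

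1. Use the same study-consent condition at all ten hospitals: giving contact details, entry of the study record, and use of outcome data.
2. At CATSystem hospitals, ask about CATSystem tracking and SMS as a separate question, after study consent.
3. Record women who accept the study but decline tracking with alerts, SMS and tracking off, as the look-alike copy in II.B already does for SOC data. State in II.C that they are analysed in the CATSystem arm, as allocated.

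Refusals are already logged at all sites (II.D). Reporting them by arm is routine and would show how large r is.

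Costs: a consent amendment through the approving boards (II.H); an alerts-off record at the five intervention hospitals for what should be a small group; and a slight dilution of the contrast, since some women in the CATSystem arm will not be tracked. That dilution belongs to the effect of allocating a hospital to the CATSystem.
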